Based on the Exploration, Preparation, Implementation, Sustainment (EPIS) framework [27], we developed the Co-Fam model together with school health services, PHC including dieticians and physiotherapists, a pediatric clinic (PC) and parents to increase acceptability and feasibility [28, 29]. Obesity treatment for children in Sweden involves a collaboration between schools run by municipalities or private corporations, and healthcare run by regional authorities [30], all publicly funded. Implementation of interventions in multi-organizational settings needs careful planning to be successful. The Co-Fam model combines the universal “Healthy School Start” (HSS) family support program delivered by school personnel in grade one with a focus on health promotion and prevention with the targeted “More and Less” (ML) obesity treatment program offering parental group sessions by PHC personnel. The HSS program has been evaluated for children aged 5–7 in three cluster-randomized controlled trials with beneficial effects on diet [31–33], and a significant decrease in BMI in children with obesity [12]. The more intense and targeted ML program for parents of children aged 2 to 6 years with overweight or obesity has shown clinical effectiveness in two randomized controlled trials [13, 34, 35]. In order to maintain and enhance the weight change seen in the HSS program for children with higher needs, the ML program could be effective. Accordingly, the Co-Fam model builds on a combination of the HSS and ML program. This requires adaptation of ML for parents of children aged 6 to 12, for whom evidence-based parental support is not available in Sweden. The Co-Fam model is novel in the since that it integrates these two programs across settings and levels of care, creating a coherent pathway from universal prevention to targeted treatment according to child needs.

We hypothesize that combining the HSS and ML programs in a coherent model will be feasible and acceptable, increase health literacy, ensure early identification of families in need, and enable early treatment of overweight and obesity. In addition, we hypothesize that it will lead to better collaboration between school health services, primary and specialized healthcare, ultimately improving prevention and treatment of children with overweight and obesity. This study aims to evaluate both the effectiveness of the ML program and implementation of the Co-Fam model in the Swedish context.

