The specific research questions are:

What is the effectiveness of the 12-month ML program on children’s weight development, compared to standard care for overweight and obesity in 6 to12 year-old children?What are the effects of the ML program on children’s diet, eating behavior, physical activity and on parental feeding practices, compared to standard care?Is the Co-Fam model acceptable, feasible, and cost-effective?

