### Study design

In this hybrid type 2 effectiveness-implementation study [36] with two parallel arms, children aged 6–12 years with overweight or obesity will be randomized to either the ML program or standard care. The universal HSS program has been running in primary schools in the municipality since 2022. The intervention arm will receive the ML program adapted to children 6–12 years by the researchers who developed the program who are part of the research team (PN and AE). The control arm will receive standard care for overweight or obesity. Both arms are followed over a period of 12 months. Personnel from school health services, PHC, and PC will be involved in recruitment, implementation and follow-up. PHC personnel, mainly dieticians and physiotherapists, have been trained as group leaders and will deliver the ML program to parents.

The study will be conducted in line with the ethical principles for medical research involving human subjects in the Declaration of Helsinki [37]. This protocol was developed in accordance with the

Standard Protocol Items: Recommendations for Intervention Trials (SPIRIT) guidelines [38]. The intervention is reported using the template for intervention description and replication (TIDieR) [39] checklist. The guidelines are presented in Supplementary Table 1.

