Conduct educational outreach visits	Adherence	Number of outreach visits and attendance	Checklist by researchers
	Responsiveness	Individual interviews with healthcare personnel about the usefulness, content and appreciation of the outreach visits	Interviews by researchers

*Abbreviations:**HCP* Healthcare personnel, *ML* More and Less

Acceptability is the perception among stakeholders that a given treatment, service, practice, or innovation is agreeable, palatable, or satisfactory [72], while feasibility is the extent to which a new treatment or an innovation can be successfully used or carried out in a given setting [72]. Acceptability and feasibility will be evaluated with individual interviews with approximately two to three parents from each ML group (total ~ 16 parents) three to 12-months after start, and with providers at the end of the 24-month follow-up.

A health economic evaluation of the Co-Fam model will be conducted using a cost-utility design, applying a decision tree and Markov model over a lifetime horizon. The model will be driven by changes in BMI resulting from the trial. Costs will be obtained from the Co-Fam model and the ML program, supplemented with data from the literature and other publicly available sources. Additional parameters, including transition probabilities and utility weights for different health statuses will be derived from both the literature and intervention data. Quality-adjusted life years (QALY) will serve as the measure for utility. Cost-effectiveness will be expressed as an incremental cost-effectiveness ratio (ICER). Sensitivity analyses will be performed to assess the robustness of the results to plausible variations in key parameters and assumptions.

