## Discussion

The Co-Fam model combines two evidence-based programs that align with the recommended components for supporting families with children aged 6–12 years, namely being theory-based, focusing on parenting practices and role modelling, and using a person-centered approach, as outlined in the national guidelines for treatment of overweight and obesity in children [25]. Parents exert a key influence on the home-food environment and on the opportunities available for children to be physically active. Thus, support for parents to facilitate healthy habits needs to be strengthened, especially for parents born outside of the Nordic region whose children have a higher prevalence of overweight and obesity than Nordic-born [4]. Furthermore, targeting children before entering puberty has been found to be more effective on future weight development than in older children [23]. Since structured evidence-based parental support programs for children 6–12 years with overweight and obesity are lacking in Swedish healthcare today, many families do not get the recommended support. Thus, if shown to be feasible and effective, the Co-Fam model will provide an evidence-based approach to preventing and treating unhealthy behaviors and overweight and obesity in children [25].

Families with children attending public school in the municipality automatically receive the HSS program, which is integrated into the school’s curriculum and has been successfully delivered since 2022. As the program is delivered during regular classes, families cannot opt out. However, for participation in the ML program, both parents and the child must provide consent. Both parents are encouraged to participate to support consistency in parenting practices. Children will be informed about the study by their parents and asked to consent to the measurements of height, weight and waist circumference which are taken by the school nurse. School nurses are responsible for student health and routinely perform these measurements as part of national follow-ups. Therefore, collecting measurements in this context is considered the least intrusive approach.

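### The cost-utility analysis is of Co-Fam (HSS plus ML), but its effect input comes from a trial that randomises only ML, so a trial-based ICER can describe ML only

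*Protocol article*

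**What the plan says.** The third research question (Background) reads "Is the Co-Fam model acceptable, feasible, and cost-effective", and the Abstract lists cost-effectiveness of Co-Fam within the dual primary aim. The economic paragraph, under Secondary outcomes, keeps the same object: "A health economic evaluation of the Co-Fam model will be conducted using a cost-utility design". Its two key inputs are then given. For effect: "The model will be driven by changes in BMI resulting from the trial". For cost: "Costs will be obtained from the Co-Fam model and the ML program", supplemented by literature and public sources. The result is to be an ICER from a decision tree and Markov model over a lifetime horizon.

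Background defines the object: "the Co-Fam model builds on a combination of the HSS and ML program". Study design defines the randomised contrast: "children aged 6–12 years with overweight or obesity will be randomized to either the ML program or standard care". The same section says that HSS has been in the municipality's primary schools since 2022. The Discussion adds "Families with children attending public school in the municipality automatically receive the HSS program" and says that opting out is not possible.

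**The concern.** An ICER is interpretable only if its cost difference and its effect difference come from the same comparison. Here the named object is a package of two programmes, while the named effect source isolates one of them. HSS exposure does not depend on the arm, so any HSS effect on BMI is balanced by randomisation and drops out of the arm difference.

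What is at stake is the conclusion on value for money. The Abstract and Discussion say that the results should inform scaling up, policy and practice. A payer who reads an ICER labelled Co-Fam would take it as evidence for funding HSS and ML together, although the trial tests ML alone. The randomised effect estimate itself is not affected.

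**Working it through.** The article states no cost, QALY or ICER figure, so there is nothing to reproduce. The check sets the comparison that the question needs against the one that the trial gives, and then tries each way of handling HSS costs.

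**Effect side.** Write Q(a, h) for expected QALYs under treatment a (ML, or standard care SC) and HSS status h.

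- The trial supplies: Q(ML, HSS) − Q(SC, HSS).
- A comparison of Co-Fam with neither programme needs: Q(ML, HSS) − Q(SC, no HSS).
- The second equals the first plus [Q(SC, HSS) − Q(SC, no HSS)].

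The bracketed term is the HSS effect, and the trial does not identify it. The article has reason to think that it is not zero: Background reports a BMI decrease in children with obesity from earlier HSS evaluation. Children without overweight also receive HSS but are not enrolled, so any benefit to them is outside the trial too. The economic paragraph draws transition probabilities, utility weights and some costs from the literature, but names no source for an HSS effect on BMI.

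**Cost side.** Let C_ML, C_SC and C_HSS be costs per child, and ΔQ the trial-based QALY difference.

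- HSS costed in both arms: (C_ML + C_HSS) − (C_SC + C_HSS) = C_ML − C_SC. The multiplier on the ICER is 1.00. Cost and effect match, and the result is for ML versus standard care.
- HSS costed in neither arm: again C_ML − C_SC, with the same result.
- HSS costed on the ML side only: C_ML + C_HSS − C_SC. Divided by C_ML − C_SC, the multiplier is 1 + C_HSS/(C_ML − C_SC). A cost enters without its benefit.
- Co-Fam costs read as coordination and implementation costs only: C_ML + C_coord − C_SC. The result is for ML with its coordination versus standard care.

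None of these four turns ΔQ into the effect of Co-Fam as the article defines it.

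**Size under one-sided costing.** This rests entirely on an assumed ratio C_HSS/(C_ML − C_SC), with a positive incremental cost and a positive ΔQ:

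| Assumed ratio | Multiplier |
|---|---|
| 0.05 | 1.05 |
| 0.25 | 1.25 |
| 0.50 | 1.50 |
| 1.00 | 2.00 |

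The table only restates the assumption (1 + ratio). It shows direction and is not an estimate for this trial.

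**Two side checks.** HSS is a grade-one programme in public schools since 2022, so some older or private-school children in the trial will not have had it. That makes the setting mixed, but it does not make HSS exposure depend on the arm. The BORIS register group is not named as the economic comparator. It covers obesity only and is matched on baseline BMI z-score, so it would not recover an earlier HSS effect.

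**The case against.** A reader might infer that the plan charges HSS costs to the intervention arm alone and so produces an inflated ICER. The article does not support that. The cost sentence names data sources; it does not mention HSS costs, assign any cost to an arm or define the increment. An incremental ratio drops costs common to both arms, and with equal HSS costing there is no distortion.

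The cost sentence also lists Co-Fam and ML as two sources. That would be redundant if Co-Fam there meant HSS plus ML, so the Co-Fam costs may be those of training, learning collaborative, newsletters and outreach. The section on implementation of the Co-Fam model points the same way: it separates effectiveness of ML from implementation of Co-Fam and says that HSS has been evaluated before. Finally, one paragraph in a journal article cannot carry the whole economic plan, and the evaluation sits under secondary outcomes, with fidelity as the primary implementation outcome.

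Most of this stands. Inflation is conditional, its size is unknown, and missing details such as perspective or cost allocation are no fault in an article. What it does not answer is the mismatch in what the article does state. The object is Co-Fam, Background defines Co-Fam as HSS plus ML, and the effect driver is a contrast of ML with standard care. The coordination-cost reading leaves that mismatch in place.

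**Conclusion.** The point holds as a mismatch between the stated object of the cost-utility analysis and its stated effect source. Followed as written, the plan gives an ICER that is valid for ML versus standard care but labelled as Co-Fam. Under one-sided HSS costing, which is neither stated nor excluded, the ICER would be inflated by 1 + C_HSS/(C_ML − C_SC). No figure can be attached, because the documents give no costs.

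The stronger statement, that the ICER is biased as planned, is not established. The conclusion rests on two things in the text: Co-Fam includes HSS, and HSS exposure is not varied by randomisation. It does not require that every trial child has had HSS. It bears on what can be concluded about cost-effectiveness, and not on the trial's BMI result.

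**What to change.** In the economic paragraph under Secondary outcomes, define the trial-based base case as ML, with its implementation and coordination costs, versus standard care in a setting where HSS is in place. State that HSS costs are equal in both arms and outside the increment. Label the ICER and its conclusion as ML versus standard care. Treatment visits are already to be taken from medical records (Data collection), so the standard-care side of the increment has a source.

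If a whole-model Co-Fam ICER is wanted, report it as a separate scenario, labelled as modelled, that includes both the HSS cost and an HSS effect taken from its own cluster-randomised trials. Align the cost-effectiveness part of the third research question; its acceptability and feasibility parts can stay with Co-Fam.

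This needs no new trial data. It costs rewording, a little more modelling if the scenario is kept, and a narrower headline claim. The statistical analysis plan is still to be finalised before data collection ends, so it can be settled there before results are known.

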### Data collection

Data collection activities, time points, and data sources are shown in Table 4. Children’s height, weight, and waist circumference will be measured by the school nurse at three timepoints. Parents will answer a baseline questionnaire including demographic data (sex, age, country of birth, years in Sweden, education, housing situation, employment status, weight, height, number of children) and their child (sex, age, country of birth, school, treatment clinic, additional diagnoses). Questionnaires regarding the child’s diet and physical activity habits, the child’s eating behavior, and parental feeding practices are included in the three assessments. Questionnaires can be answered from a mobile phone/tablet/computer, at a convenient time for the participant. Data regarding number of treatment visits and comorbidities will be collected from the child’s medical journal. Data on implementation outcomes will be collected from parents and HCPs via questionnaires distributed during the study period and semi-structured interviews performed after participation in the ML program. Data from the BORIS registry [55] will be collected retrospectively.

**Table 4 Tab4:** Data collection and time points

TIMEPOINT	Enrollment and randomization	TRIAL PERIOD		
	Pre-intervention	T0	T1	T2
ENROLLMENT:	X			
Eligibility screen	X			
Informed consent	X			
Randomization	X			
INTERVENTION/COMPARATOR:				
* Intervention: More and Less*		X	X	X
* Comparator: Standard care*		X	X	X
* Comparator: Register control*		X	X	X
ASSESSMENTS: Effectiveness outcomes				
* Child’s eating habits*		X	X	X
* Child’s physical activity*		X	X	X
* Child’s eating behavior*		X	X	X
* Parental feeding practices*		X	X	X
* Child’s weight*,* height and waist*		X	X	X
ASSESSMENTS				
* Demographics*		X		
* Adverse events*			X*	X*
* Fidelity*			X	X
* Feasibility*				X
* Acceptability*				X
* Cost*				X

*Data on adverse events is collected continuously. Abbreviations: T0, baseline; T1, 3-month follow-up, T2, 12-month follow-up

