**Fig. 1 Fig1:**
[figure not shown]
The Co-Fam model

The HSS program has been provided in grade one to all children and their families attending public schools in this municipality since 2022. The program is based on Social Cognitive Theory [19] and consists of four components: (1) A parental guide with health information available in 11 languages; (2) a motivational interview with parents performed by the school nurse; (3) classroom activities for the children performed by teachers with home assignments; and (4) a T2D risk self-assessment test for parents [44]. For a detailed description of the HSS program see Elinder et al. [45]. The HSS program has been evaluated regarding implementation showing that the program can be performed with relatively high fidelity, although somewhat lower in families with a non-Nordic background mainly due to language issues when performing the motivational interview [46]. Qualitative studies with school personnel and families have shown that teachers, school nurses, parents and children overall have a positive attitude towards the program and that it has raised the health literacy of the participants in both theory and practice [47–50].

The ML parental support program is grounded in Social Learning Theory [51, 52] and Social Interaction Learning Theory [19, 51] which together emphasize how parenting practices, social interactions, and broader environmental contexts influence children’s behaviors [53]. The ML program is based on a manual and consists of ten weekly 90-minute group sessions, led by primary healthcare personnel (HCP) (dieticians and physiotherapists) trained as group leaders (Table 2). The group sessions are followed by six individual booster sessions every six weeks for another nine months. Group sessions focus on strengthening parent-child communication to achieve healthy behaviors through evidence-based parenting practices, including positive reinforcement and role modeling, with role play and peer discussions as key components for building skills. Parents receive handouts briefly outlining the content of each session, including home assignments. The booster sessions focus on the families’ individual needs and provide an opportunity to follow up on the relevant topics covered during the group sessions.

**Table 2 Tab2:** Content of the group sessions in the More and Less parental support program (month 1–3)

Session	Topic	Content overview

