### The implementation strategies

The strategy *Conduct ongoing training* is a four-day course for HCPs in the ML program based on a manual, including supervision and feedback. The strategy *Prepare parents to be active participants* includes HCPs providing information to families meeting the inclusion criteria about consequences of overweight in children and the ML program. The strategy *Intervene with parents to enhance uptake and adherence* includes HCPs distributing information leaflets in different languages to support recruitment and contact with civil organizations within the community to increase uptake of hard-to-reach groups. The strategy *Create a learning collaborative* includes meetings of the research team together with HCPs from PHC and school health services every six months to discuss study progress and potential problems. The strategy *Promote adaptability* enables revision of strategies if needed (while keeping the intervention components intact), to be agreed on during the learning collaborative meetings. The strategies *Remind clinicians* and *Conduct educational outreach visits* aim to support HCPs during implementation. Reminders include newsletters sent four times per year with updates about the study and useful tips for recruitment and meetings with families. Outreach visits include inspirational lectures for HCP on two occasions per year. Implementation strategies are described in more detail elsewhere [29].

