### Randomization

When parents have signed the consent form, they will be randomized to a treatment arm using REDCap randomization module [61]. A block randomization with a block size of six will be used to ensure a balanced allocation across treatment arms within each stratum. Stratification into the two strata overweight and obesity will be performed based on the baseline BMI z-score. Each block of six will have three participants in the intervention arm and three in the control arm, and the order of assignments within each block will be random. To include 126 participants, 21 blocks are needed. A research assistant will inform the clinics about which arm the participant belongs to. Neither HCPs nor parents will be blinded to allocation. The statistician remains blinded to group allocation until the analyses are performed to ensure objectivity. HCPs will not have access to the random allocation sequence.

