## Abbreviations

BMI: Body Mass Index
COM-B: Capability, Opportunity, Motivation and Behaviour
EPIS: The exploration, preparation, implementation, sustainment
ERIC: Expert Recommendations for Implementing Change
HCP: Healthcare Personnel
HSS: Healthy School Start
ICER: Incremental cost-effectiveness ratio
IOTF: International Obesity Task Force
IRLM: Implementation Research Logic Model
ML: More and Less
PC: Pediatric clinic
PHC: Primary Healthcare
QALY: Quality-Adjusted Life-Year
RCT: Randomized Controlled Trial
SPIRIT: Standard protocol items for clinical trials
TDF: Theoretical Domains Framework
TIDier: Template for intervention description and replication
T2D: Type 2 diabetes

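### The school nurses who measure height, weight and waist are not protected from knowing the arm, although delivering the trial does not require them to know it

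*Protocol article*

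**What the plan says.** **Who measures.** The Data collection section says that children's height, weight and "waist circumference will be measured by the school nurse at three timepoints". The Discussion repeats this, referring to "measurements of height, weight and waist circumference which are taken by the school nurse", and gives the reason: nurses do this routinely, and it is judged the least intrusive option.

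**Who is blinded.** The Randomization section says "Neither HCPs nor parents will be blinded to allocation". The only blinding it provides is for the analysis: "The statistician remains blinded to group allocation until the analyses are performed to ensure objectivity". It adds that a research assistant tells the clinics which arm a participant is in. Schools are not mentioned there.

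**Who counts as an HCP.** Usage varies.
- The implementation strategies section describes "meetings of the research team together with HCPs from PHC and school health services every six months", which places school health services among HCPs.
- The Abbreviations list gives the general expansion "HCP: Healthcare Personnel".
- The Co-Fam model section (below Fig. 1) is narrower: ML groups are "led by primary healthcare personnel (HCP) (dieticians and physiotherapists) trained as group leaders".
- Table 3 names school nurses separately from HCPs.

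**Other roles of school health services.** They identify eligible children and inform parents about the study (Recruitment section). Their personnel take part in recruitment, implementation and follow-up (Study design), and a school nurse's finding starts a referral (Study setting).

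**The concern.** Parents and providers cannot realistically be blinded in a trial of parent groups against standard care, so masking the person who measures is the main safeguard still available for the primary outcome. The article sets out who measures, who is blinded and who is not, and nothing in it keeps the allocation from the measurer. The nurses are not detached assessors either: they help to find and inform families, and their service attends the six-monthly study meetings. Unblinded families can also mention the arm at a measurement visit.

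If a nurse knows the arm, small differences in posture, in allowance for clothing or in rounding could differ between arms. The target difference is only 0.16 BMI z, so a small arm-dependent shift would matter. The same readings feed the secondary BMI z-score cut-offs and the waist-to-height ratio, and the health-economic model is driven by the trial's BMI changes. A biased reading cannot be corrected at analysis, so this has to be settled in trial conduct and cannot be left to the statistical analysis plan.

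**Working it through.** **1. The plan's own sample size.** Inputs from the Sample size section: difference 0.16, SD 0.3, 80% power, alpha 0.05, 10% loss.

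n per arm = 2 × 0.3² × (1.960 + 0.842)² / 0.16² = 55.2, rounded up to 56. Allowing for loss: 56 / 0.9 = 62.2, rounded up to 63 per arm, or 126 in total. The stated figure reproduces with a two-sided test. A one-sided test would need only 44 per arm before loss.

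**2. Precision of the 12-month comparison.** With 56 analysed per arm, SE = 0.3 × √(2/56) = 0.0567. Power at 0.16 is Φ(0.16/0.0567 − 1.960) = 80.6%.

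**3. Illustration of an arm-dependent shift.** The documents give no size for such a shift, so b is assumed. When there is no true effect and b favours ML:

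type I error = Φ(b/SE − 1.960) + Φ(−b/SE − 1.960)

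When the true effect is 0.16 and b works against ML:

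power = Φ((0.16 − b)/SE − 1.960)

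| Assumed b (BMI z) | Share of 0.16 | Two-sided type I error | Power if b is against ML |
|---|---|---|---|
| 0 | 0% | 5.0% | 80.6% |
| 0.02 | 12.5% | 6.4% | 69.5% |
| 0.05 | 31% | 14.3% | 49.2% |

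**4. What the planned model does with a constant error.** The Data analysis section estimates a treatment-by-linear-time slope over months 0, 3 and 12. Take baseline as unaffected, data as complete, and an error e at both follow-ups in one arm. The mean time is 5, the deviations are −5, −2 and 7, and their squares sum to 78. The slope bias is (−2e + 7e)/78 = 5e/78 per month, which over 12 months is 60e/78 = 0.77e. On that scale, shifts of 0.02 to 0.05 correspond to reading errors of about 0.026 to 0.065 (0.02/0.77 and 0.05/0.77). The table uses the simple 12-month comparison from the Sample size section, so it indicates scale and is not a simulation of the planned model.

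**5. Can the text settle whether the nurse is blinded?** The Randomization sentence, read with the implementation strategies section and the Abbreviations list, includes school nurses among the unblinded. Read with the Co-Fam model section and Table 3, it does not. No passage says the nurse is told the arm, and none says the nurse is kept from it.

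**The case against.** The strongest reply is that the nurses may never learn the arm. Only the clinics are said to be informed, the Study setting section says school health services often have no easy access to treatment information, and ML is delivered by primary healthcare staff and not by the measuring nurses. The learning-collaborative meetings are described as covering progress and problems, with no mention of individual children. Height and weight are fairly objective. Waist depends more on the operator, but it enters only the secondary waist-to-height ratio. Randomization is by child, so a nurse's habitual technique falls on both arms alike, and only technique that changes with the arm biases the comparison.

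All of this stands, and it limits the finding in two ways.
- A reader might infer from the HCP sentence that the measuring nurses are known to be unblinded. The inconsistent use of the term does not support that.
- A reader might convert a centimetre of height or half a kilogram of clothing into z units and conclude that bias could take up most of the 0.16 target. The documents give no such conversion, and the argument needs the whole error to fall in one arm.

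What the reply does not do is point to any provision that keeps the allocation from the nurse. Informing the clinics is not the same as informing only the clinics, and families remain free to disclose. The article's silence on a detailed measuring procedure is no fault, since such detail normally sits in a manual.

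**Conclusion.** The point holds as a gap in protection. The people who take the readings behind both primary outcomes also help to recruit, and nothing in the plan keeps the allocation from them, although neither arm's delivery requires them to have it. The plan does not establish that they are unblinded, and it does not show that any bias will occur.

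The size is illustrative only. It rests on an assumed shift of 0.02 to 0.05 BMI z in the 12-month comparison, SD 0.3, 56 analysed per arm and a normal approximation. Under those assumptions, type I error rises to about 6% to 14% if the shift favours ML, and power falls to about 70% to 49% if it goes the other way. Neither size nor direction can be derived from the documents. This is an inexpensive improvement worth making before follow-up measurements begin. It is not a flaw that invalidates the design, and the sample size does not change.

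**What to change.** Keep measurement by school nurses, which preserves the reason given in the Discussion, and make these changes:

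- In the Randomization and Data collection sections, state that allocation is sent to the treating clinics only and not to the school nurse who measures. This also settles whether the unblinded HCPs include the measurer.
- Ask families not to disclose their arm at the 3- and 12-month measurements.
- Keep child-level allocation out of the learning-collaborative meetings.
- At T1 and T2, record whether the nurse knew the arm, and report this descriptively by arm. Do not build an adjusted or subgroup analysis on it: it arises after randomization and may differ by arm if ML families disclose more often.

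Cost: some wording, an instruction to families and one extra data item at two time points. No extra staff or participants should be needed; that is a judgement, as the documents give no costs. The downsides are that some nurses will still learn the arm, and that the nurse cannot use the allocation to coordinate care around the measurements.
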